# The benefits and tolerance of exercise in myasthenia gravis (MGEX): study protocol for a randomised controlled trial

**DOI:** 10.1186/s13063-017-2433-2

**Published:** 2018-01-18

**Keywords:** Myasthenia gravis, Physical exercise, Quality of life

## Abstract

**Background:**

Research exploring the effects of physical exercise in auto-immune myasthenia gravis (MG) is scarce. The few existing studies present methodological shortcomings limiting the conclusions and generalisability of results. It is hypothesised that exercise could have positive physical, psychological as well as immunomodulatory effects and may be a beneficial addition to current pharmacological management of this chronic disease. The aim of this study is to evaluate the benefits on perceived quality of life (QOL) and physical fitness of a home-based physical exercise program compared to usual care, for patients with stabilised, generalised auto-immune MG.

**Methods:**

MGEX is a multi-centre, interventional, randomised, single-blind, two-arm parallel group, controlled trial. Forty-two patients will be recruited, aged 18–70 years. Following a three-month observation period, patients will be randomised into a control or experimental group. The experimental group will undertake a 40-min home-based physical exercise program using a rowing machine, three times a week for three months, as an add-on to usual care. The control group will receive usual care with no additional treatment. All patients will be followed up for a further three months. The primary outcome is the mean change in *MGQOL-15-F* score between three and six months (i.e. pre-intervention and immediately post-intervention periods). The *MGQOL-15-F* is an MG-specific patient-reported QOL questionnaire. Secondary outcomes include the evaluation of deficits and functional limitations via MG-specific clinical scores (Myasthenia Muscle Score and MG-Activities of Daily Living scale), muscle force and fatigue, respiratory function, free-living physical activity as well as evaluations of anxiety, depression, self-esteem and overall QOL with the WHO-QOL BREF questionnaire. Exercise workload will be assessed as well as multiple safety measures (ECG, biological markers, medication type and dosage and any disease exacerbation or crisis).

**Discussion:**

This is the largest randomised controlled trial to date evaluating the benefits and tolerance of physical exercise in this patient population. The comprehensive evaluations using standardised outcome measures should provide much awaited information for both patients and the scientific community. This study is ongoing.

**Trial registration:**

ClinicalTrials.gov, NCT02066519. Registered on 13 January 2014.

**Electronic supplementary material:**

The online version of this article (10.1186/s13063-017-2433-2) contains supplementary material, which is available to authorized users.

## Background

Auto-immune myasthenia gravis (MG) is a rare, chronic, auto-immune disease of the neuromuscular junction. The incidence is estimated to be 30 per 1,000,000 people per year worldwide [1]. MG affects both genders and symptoms include fluctuating fatigue and weakness which vary in intensity and location (upper and/or lower limbs, axial, eyes and face, bulbar and respiratory muscles) [2]. These symptoms affect patients to varying degrees and while disease-induced mortality is rare nowadays, activities of daily function are affected and quality of life (QOL) is reduced [3–6]. Relapses are unpredictable and can be present throughout the disease course, especially in the initial stages when the disease may not yet be treated. Current treatment includes various pharmacological agents which are either symptomatic such as acetylcholinesterase inhibitors which act to temporarily relieve symptoms or disease-modifying immunosuppressors aimed at minimising the auto-immune response. As there is currently no known cure, the goal of treatment is to obtain remission; and where this is not possible, to obtain disease stability with the least symptoms.

While rest is recommended during an acute exacerbation of MG, evidence is lacking as to whether exercise is both feasible and beneficial in periods of disease stability. Anecdotal evidence from patients with MG suggests that those who participate in regular physical exercise feel better. According to them, it gives them confidence in their capacities and helps them understand their disease and their personal limits. Some even report experiencing symptom improvement and reduced levels of fatigue [7].

For the general population, it is widely accepted that regular physical exercise has multiple positive physical and psychological effects as well as being effective in the prevention of various non-communicable diseases such as stroke, heart disease and cancer and increasing longevity [8–10]. Recently, the use of exercise has been proposed in the management of various neurological diseases [11–13]. Exercise has even been compared to pharmacological treatment and has been found to be equivalent in some populations, supporting the recent notion that ‘exercise is medicine’ [14]. Traditionally, exercise was thought to exacerbate symptoms for patients suffering from MG as their muscle weakness and fatigue was thought to be brought on or worsened by physical exertion and improved with rest. Despite the increasing number of studies exploring exercise in various neuromuscular pathologies, to date, little research has explored physical activity in the context of MG [15, 16]. Several case studies exist which demonstrate that despite the disease patients can participate in sport and increase their strength, power or endurance with adequate training [17–20]. A within-subject control study provided promising results, yet these limited data do not enable us to draw reliable conclusions concerning the safety and benefits of physical exercise for patients with MG [21]. Two new studies provide further information including different types of physical exercise [22, 23]. In the study by Rahbek et al., progressive resistance training appears to be beneficial however aerobic training seems to increase depression and fatigue and reduce knee extensor strength [22]. The mixed aerobic resistance program study carried out by Westerberg improved functional physical performance and exercise self-efficacy without strength improvements noted [23]. Exercise was well tolerated in both studies; however, due to small sample sizes and lack of control group, it is difficult to make firm conclusions about the various possible benefits. It is hypothesised that physical exercise is beneficial for adults with stabilised MG.

The primary aim of this study is to determine whether a regular moderate intensity physical exercise program improves perceived QOL for patients with stable, generalised MG. Secondary aims are to evaluate the effects of this exercise program compared to usual care on physical fitness, depression and self-esteem as well as on the immune system.

## Methods/Design

### Study design, ethics, consent and permission

This is a multi-centre, interventional, randomised, single-blind, parallel group, controlled trial with a planned duration of four years (nine months for each patient) (Figs. 1 and 2).

**Fig 1 Fig1:**
[figure not shown]
CONSORT *flow diagram* of the MGEX study

**Fig 2 Fig2:**
[figure not shown]
Standard protocol items recommendations for interventional trials (SPIRIT). Schedule of enrolment, intervention and assessments. M0 includes enrolment and informed consent signing. Visits are monthly (M). Randomisation and allocation takes place following the 3-month visit (M3). Intervention period is 3–6 months. Post-intervention evaluation is at M6. *Evaluator blinded to treatment allocation

Safety evaluations are monthly; muscular and psychological evaluations are three-monthly (M0, M3, M6 and M9). The intervention period is between M3 and M6. The study has been approved by an ethics committee in accordance with French regulations (*Comité de Protection des Personnes Ile de France XI* under the CPP number #13064 on 13 December 2013 and authorised by the *Agence National de Sécurité du Médicament et des produits de santé* on 11 October 2013). The trial is conducted in accordance with the Helsinki Declaration [24]. Each participating patient receives written and verbal explanations about the study and evaluation procedures. The trial is registered in the ClinicalTrials.gov registry (NCT02066519). Reporting of the study will adhere to the Consolidated Standards of Reporting Trials (CONSORT) guidelines and the Standard Protocol Items: Recommendations for Interventional Trials (SPIRIT) [25–27]. The SPIRIT checklist is available as an Additional file 1.

Participating centres include the neuromuscular and neurological intensive care departments, Pitié-Salpêtrière Hospital, Paris, the Raymond Poincaré Hospital, Garches (Paris region) and Rothschild Hospital, Paris.

### Sample size calculation

We estimated that 42 patients (21 in each arm with 1:1 randomisation) would be necessary to show a difference in changes in the *MGQOL-15-F* of 8 points between both arms with 80% power and a two-sided type I error rate of 5%, assuming the standard deviation of changes in the *MQGOL-15-F* is 9 points based on Burns et al. [28]. A difference in 8 points is considered to be a clinically meaningful change for this population. No increase in sample size for potential drop-outs was considered in the calculation.

### Recruitment and trial participants

All patients presenting for a regular out-patient consultation with their neurologist in one of two university hospitals in Île-de-France, France (Pitié-Salpêtrière, Paris and Raymond Poincaré, Garches), are screened for eligibility. Both hospitals are specialist centres for the management of MG. Eligible patients are invited to participate and a date is organised for study inclusion. Information about the study is also advertised by the French Association against Neuromuscular Disorders (AFM) myasthenia group and various social media patient groups. Information flyers are displayed in the two university hospital waiting rooms.

Adult patients with a diagnosis of mild or moderate generalised MG (II or III on the Myasthenia Gravis Foundation of America [MGFA] classification) are considered for eligibility [29]. Diagnosis should be confirmed by the presence of circulating antibodies against acetylcholine (AChR) or muscle-specific kinase (MuSK) or low density lipoprotein receptor-related protein 4 (LRP4) receptors or abnormal repetitive nerve stimulation testing (decrement > 10%) on EMG or abnormal single fibre EMG (conduction block or jitter) or based on their clinical history and symptom improvement with acetylcholinesterase inhibitors. The MG must be stabilised for at least six months before entry into the study; thus, duration of the disease must be at least six months but is otherwise unrestricted. Both men and women aged 18–70 years are eligible for inclusion. For practical reasons (due to multiple visits and rowing machine delivery), participants should live in Paris or in the surrounding Paris region; they agree to be able to participate in the exercise program and can house the rowing machine for the three-month duration in their home. They should be affiliated with the national social security system.

Exclusion/non-inclusion criteria:

Patients participating in other interventional clinical trials in the preceding three months, patients for whom intensive physical exercise would be contraindicated because of unstable coronary syndrome or myocardial infarction within the preceding three months, respiratory failure (vital capacity < 70% predicted value) or cardiac failure (ejection fraction < 50% predicted value), other neuromuscular pathology, disabling rheumatological disease (> 80% disability on the Barthel scale), chronic pain or disabling orthopaedic conditions, hospitalisation in the last three months for a serious medical or surgical condition, anaemia (haematocrit < 30%), stroke within the previous year. Pregnancy or patients with pure ocular or severe MG (MGFA class I, IV or V) or with severe cognitive impairment necessitating specific protection are not eligible for inclusion, nor are patients with a score < 15 on the *MGQOL-15-F*.

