**Fig 3 Fig3:**
[figure not shown]
Theoretical profile of a training session

Each 40-min moderate intensity training session consists of a 10-min warm-up to reach their individual target heart rate (i.e. 70% of their maximal heart rate [HR], using 220-age as HRmax), followed by an endurance plateau phase consisting of 20 min of constant aerobic activity rowing at their individual target heart rate, followed by a power interval phase (ten pulls at maximum effort every minute for 5 min) and finally a 5-min active cool-down period whereby the rowing exercise is continued at a slow pace. A heart rate monitor (Garmin®) is worn by the patient and data (rowing distance, session duration, HR) are recorded by the rowing machine for each training session. These will be analysed to evaluate tolerance and possible cardiovascular adaptations from exercising. Patients are advised to organise their training sessions on alternate days. The first home session is supervised when possible. Details will be presented as per current recommendations for reporting of exercise interventions [30]. Patients continue to benefit from usual care.

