### Adverse event reporting

An adverse event (AE) is defined as any untoward medical occurrence in a participant which does not necessarily have a causal relationship with this study. These can be identified at any moment during the study. Eligibility criteria rule out patients with known contraindications to physical exercise. An ECG is performed monthly to monitor cardiac status. It is expected that patients in the experimental group may experience muscle soreness and fatigue in response to exercise, particularly for the more sedentary patients. However, this is not an AE as it is considered a normal response to exercise.

A serious adverse event (SAE) includes: death; risk of death; necessity or prolongation of existing hospitalisation; persistent or significant disability or incapacity; or any other undesirable event considered to be medically significant. MG exacerbation requiring modification of current therapeutic management during the intervention period is considered a possible AE. All suspected unexpected SAEs are to be notified without delay to the sponsor, as well as any worsening of the disease suspected to be related to the physical programme if a patients' treatment needs to be modified. In this case, unblinding can occur. Should a worsening occur without needing a change of the treatment, it is only to be recorded in the electronic database without mandating a direct report to the sponsor. The sponsor’s vigilance unit is in charge of the causality assessment as well as of its regulatory duties with regard to reporting obligations to the French Medicines Agency.

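### The cardiac-failure exclusion gives ejection fraction as a percentage of a predicted value, a unit that does not fit the measure and leaves the threshold open to two readings

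*Protocol article*

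**What the plan says.** Under Recruitment and trial participants, the exclusion list covers "patients for whom intensive physical exercise would be contraindicated because of unstable coronary syndrome" or recent myocardial infarction, and continues with respiratory and cardiac failure. Each of those last two has a threshold in brackets: "respiratory failure (vital capacity < 70% predicted value"), then "cardiac failure (ejection fraction < 50% predicted value"). The article gives no predicted ejection fraction or reference equation, and does not restate the threshold elsewhere.

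The Intervention section calls the session moderate in intensity but includes a power phase of "ten pulls at maximum effort every minute for 5 min". After two to three supervised learning sessions, patients train at home.

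Adverse event reporting relies on the exclusion list: "Eligibility criteria rule out patients with known contraindications to physical exercise". The same section adds a monitoring measure: "An ECG is performed monthly to monitor cardiac status".

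**The concern.** Vital capacity is a volume that depends on body size, age and sex, so a percentage of a predicted value is a natural scale for it. Ejection fraction is by definition a proportion, the share of the ventricular volume ejected, and is already expressed as a percentage. Repeating the vital-capacity unit after it looks like a carry-over, and it leaves a screener with two ways to apply the rule.

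At stake is who may enter a home exercise programme with maximal-effort intervals, in patients up to age 70. The bracket is the only operational definition of cardiac failure in the article, and tolerance of exercise is one of the trial's headline questions. Two hospitals recruit. If they read the bracket differently, they admit different populations. In a trial of 42, even one patient classified differently could affect the safety account.

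**Working it through.** **Inputs from the article.** Ejection-fraction threshold: 50%, labelled as a percentage of the predicted value. Vital-capacity threshold next to it: 70%, same label. Predicted ejection fraction: not given.

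**Input assumed.** A predicted ejection fraction of 55–70%. This is an assumption, used only to show the size of the gap.

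**Step 1: the two readings.**
- Absolute reading: exclude if ejection fraction is below 50%.
- Literal reading: exclude if ejection fraction is below 0.50 × predicted value.

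**Step 2: direction, without any assumption.** The two cut-offs coincide only if 0.50 × predicted = 50%, that is, predicted = 100%, which would mean complete emptying of the ventricle. For any predicted value below 100% the literal cut-off is lower, so the literal reading is the more permissive.

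**Step 3: size, under the assumed range.**

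| Assumed predicted value | Literal cut-off (0.50 × predicted) | Gap to an absolute 50% |
|---|---|---|
| 55% | 27.5% | 22.5 points |
| 60% | 30.0% | 20.0 points |
| 65% | 32.5% | 17.5 points |
| 70% | 35.0% | 15.0 points |

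Under the literal reading, the ejection-fraction figure alone would not exclude a patient whose value lies between about 27.5–35% and 50%. Under the absolute reading it would.

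**Step 4: link to the safety section.** The statement that eligibility removes known contraindications agrees with the opening clause of the exclusion list. Under the absolute reading there is no tension. Under the literal reading, the assurance is not secured for reduced ventricular function.

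**Step 5: effect on the design figures.** The stated sample size uses a difference of 8 points, a standard deviation of 9, two-sided 5% and 80% power. A two-sample t-test calculation gives power 0.782 with 20 per arm and 0.803 with 21 per arm, so the stated 21 per arm (42 in total) is reproduced. None of these inputs involves ejection fraction, so the figure does not change.

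**The case against.** A reader might infer that the criterion admits patients with clearly reduced ejection fraction. The article does not support that. It would require a site to apply the phrase literally and to have a predicted value to halve, and the article supplies none. A site could reasonably take the figure as an absolute 50%, in which case no additional patient enters. Nothing shows that such a patient was enrolled, and Trial status reports no exercise-related adverse events at that stage.

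A reader might also infer a contradiction between the exclusion list and the safety section. That conflict arises only under the literal reading, because the bracket sits under a clause about patients in whom intensive exercise is contraindicated. Nor is the threshold the only cardiac protection. Unstable coronary syndrome, recent infarction and recent hospitalisation for a serious condition are also excluded. A neurologist examines patients monthly with auscultation and ECG, and patients are advised to stop training if a medical contraindication arises. The first home session is supervised when possible, and weekly phone calls follow.

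Finally, the article condenses protocol V3.0, which is not shown, so the phrase may be a slip in the article and absent from the working eligibility form.

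All of this stands, and it limits the point to an ambiguous threshold. It does not remove the ambiguity. The opening clause lists its causes, and a screener who asks what counts as cardiac failure is sent back to the bracket. The other safeguards do not set a ventricular-function threshold.

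**Conclusion.** The point holds as a wording fault in a safety threshold. The unit does not fit ejection fraction, no predicted value or reference accompanies it, and two readings are possible. That the literal reading is the looser one follows from arithmetic for any predicted value below 100%. The size of the gap, 15 to 22.5 points of ejection fraction, rests on an assumed predicted value of 55–70%.

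The consequence is conditional. If the text is applied literally, the criterion might not exclude patients with reduced ventricular function, and the safety section's assurance would not be secured for them. Whether any site reads it that way cannot be told from the article. The sample size and power are unaffected. Which cut-off is clinically right is not judged here.

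**What to change.** - The sponsor states the scale and the cut-off intended for ejection fraction and corrects the unit accordingly. The percentage-of-predicted scale is kept for vital capacity only, if that is what was meant.
- The corrected criterion is reconciled with the contraindication clause that governs it and with the statement in Adverse event reporting.
- Both recruiting hospitals use the same wording, and the sponsor confirms that the full protocol and the eligibility form carry it.
- The recorded eligibility of patients already included (32 at the time of the article) is checked against the corrected wording, and any discrepancy is documented.

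The cost is a correction to one criterion and a file check. No design figure or analysis needs to be redone.

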### Randomisation, allocation and blinding

Figure 1 depicts the participants’ flow through the study according to the CONSORT guidelines [25, 26]. Figure 2 presents the timeline of assessments and intervention. Following study inclusion, there is a three-month observation period to ensure disease stability (in addition to the six-month stability required before inclusion). All consecutive participants are then randomly assigned to either the control or experimental group with a 1:1 allocation ratio as per a computer-generated randomisation schema stratified by centre using permuted blocks of randomly varying sizes. To ensure concealment, the block sizes are not disclosed. Group allocation is revealed via a computer software (CleanWeb) exclusively to the non-blinded physiotherapist once randomisation has been performed (concealed allocation). The physiotherapist then informs the patient verbally. The randomisation list was constructed prior to the beginning of the study by an off-site independent statistician with no clinical involvement in the study.

Clinical and psychological evaluations are performed by blinded assessors. As randomisation takes place three months after inclusion, the physiotherapist is unaware of group allocation for the first two evaluations (M0 and M3). Patients are informed not to disclose their allocation to their treating neurologist or psychologist. Throughout the study all participants are requested to maintain their regular lifestyle, the only difference being the three-month exercise period for the experimental group which is lacking for the control group.

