#### Strength and endurance measures

All strength and endurance measures take place in the same neuromuscular evaluation laboratory (Neuromuscular Physiology and Evaluation Lab, Institute of Myology, Pitié- Salpêtrière Hospital, Paris) by the same trained physiotherapist.

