#### Pulmonary function and respiratory strength

For all respiratory evaluations, patients are seated with a backrest and feet firmly on the floor. Forced vital capacity (FVC) is measured with a Micro Medical Spiro USB spirometer and Spida 5 software or a Vitalograph spirometer (the same spirometer is used for all evaluations for each patient). Calibration is performed according to manufacturer’s guidelines with a 3-L syringe before each evaluation. FVC in litres is measured from total lung capacity according to the ATS/ERS task force guidelines [35]. Patients are instructed to inhale completely and then exhale maximally until no more air can be expelled. For respiratory muscle strength evaluations, the MicroRPM device (Micromedical, Rochester, UK) is used. Maximal inspiratory pressure (MIP) is measured first, followed by maximal expiratory pressure (MEP). Both are expressed in cmH_2_O. MIP is measured from residual lung volume and MEP from total lung capacity [36]. All measurements are repeated three times or until maximum values are reached if the patient continues to improve and remains clinically stable (no signs of fatigue). For MEP measures, patients are asked to place their hand around the mouthpiece to minimise air leaks. A tubed mouthpiece is used for both. Strong verbal encouragement is provided for all measures. A nose clip is used for FVC. The highest value from the three trials is used in data analysis. Secondary outcome measurements involve the mean change in FVC, MIP and MEP between M3 and M6.

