#### Grip strength

Handgrip strength of the dominant hand is measured via an isometric contraction using the Myogrip dynamometer (Ateliers Laumonier, France), an electronic device specifically designed to measure grip strength in neuromuscular disorders [40]. Its handle can be adjusted to accommodate different hand sizes and the strength is displayed directly on the screen. Patients are seated on the edge of a plinth, their back in an upright position, hips and knees flexed to 90° and feet flat on the floor. The dominant arm hangs down the side of the body with the shoulder in neutral and the elbow extended. The patient is instructed to squeeze the handle as hard as possible; verbal encouragement is provided to motivate the patient to perform a maximal effort. The test is performed three times or until no further improvement. Maximal grip strength is recorded in kg. Mean change in grip strength between M3 and M6 is a secondary outcome.

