The MINI is a short, structured, clinical interview organised in diagnostic modules [49]. It enables researchers to investigate 16 axis I DSM-IV disorders according to the DSM-IV or the CIM-10. For most modules, two to four screening questions are used to rule out the diagnosis when answered negatively. Positive responses to screening questions are explored by further investigation of other diagnostic criteria. The MINI is also used to confirm the diagnosis of depression if the Beck score is ≥ 4.

Global QOL is evaluated by the WHOQOL-BREF [50]. The French translation was validated by Leplège et al. in patients with various neuromuscular diseases [51]. This self-administered questionnaire consists of 26 items (score of 0–5) and assesses QOL according to four domains: physical health; psychological health; social relationships; and environment. Myasthenia-specific QOL is evaluated by the French version of the Myasthenia Gravis QOL scale, the MGQOL-15-F as previously described (primary outcome measure) [31].

Semi-structured interviews are conducted by trained clinical psychologists to qualitatively assess the psychological impact of MG on patients’ personal, marital, social, professional life and physical activities. The interviews are recorded to be qualitatively analysed with the NVivo software 7 as it allows a thematic analysis [52]. Finally, patients are asked to draw themselves. The instructions are: ‘Can you draw yourself as you feel today?’ This drawing is analysed as a projective test and considered as an index of the representation of the body and of its investment [53].

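### Strength and endurance outcomes are measured by a physiotherapist who knows the arm at M6 and M9, with open-ended attempts for FVC, MIP, MEP and grip and a self-contradictory rule on which attempt is analysed

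*Protocol article*

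**What the plan says.** **Blinding.** The study design section states: "This is a multi-centre, interventional, randomised, single-blind, parallel group, controlled trial". Under *Randomisation, allocation and blinding*, blinded assessors are claimed for the clinical and psychological evaluations, and patients are asked not to reveal their arm to the neurologist or psychologist. The same section says: "Group allocation is revealed via a computer software (CleanWeb) exclusively to the non-blinded physiotherapist once randomisation has been performed". This person then tells the patient. It adds that "the physiotherapist is unaware of group allocation for the first two evaluations (M0 and M3").

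**Who measures.** Under *Strength and endurance measures*, all such tests are done in one laboratory "by the same trained physiotherapist". The corresponding secondary outcomes are changes from M3 to M6.

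**Attempts and encouragement.**
- FVC, MIP and MEP: "All measurements are repeated three times or until maximum values are reached if the patient continues to improve", provided the patient is stable and not tiring. The section then says: "The highest value from the three trials is used in data analysis". Encouragement is strong.
- Grip: "The test is performed three times or until no further improvement". Verbal encouragement is given.
- Biodex torque: three maximal contractions, with strong encouragement.
- 6-minute walk: a single walk, with instructions and guidance standardised to a cited guideline.

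**Psychologist visit.** Under *QOL and psychological state*, the evaluations take place in one meeting of about 90 minutes. It includes a semi-structured interview on how MG affects patients' "personal, marital, social, professional life and physical activities". The article gives no order for interview and questionnaires.

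**The concern.** Physical fitness is a named aim of the trial, and its main measures depend on effort. For these measures the pre-intervention assessor cannot know the arm and the post-intervention assessor does. Knowledge of the arm can act through two levers that the tester holds: whether to go on to another attempt, and how hard to urge the patient. If either lever is used differently by arm at M6, the change score shifts without any true effect.

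The analysed value for FVC, MIP and MEP is also not well defined. If a fourth attempt is the best, one sentence of the section implies that it counts and another implies that it does not.

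A smaller point concerns the M6 psychology visit. If the interview comes first, talk about physical activities may prime the answers on the self-report forms, or lead patients to disclose their arm.

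**Working it through.** **1. The blinding statements set side by side.**
- Allocation is made after M3 and goes to the physiotherapist, whom the article itself calls non-blinded.
- That physiotherapist is stated to be unaware at M0 and M3. M6 and M9 are left out of that statement.
- One physiotherapist takes every strength and endurance measure. No second, blinded physiotherapist is mentioned.
- It follows that M3 is blind and M6 and M9 are not. This is a strong inference, not an explicit statement. Figure 2 marks the blinded evaluations but is not shown.

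**2. Which outcomes are open to which lever.**

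| Outcome | Tester knows arm at M6 | Attempts open-ended | Encouragement described as standardised |
|---|---|---|---|
| FVC, MIP, MEP | yes | yes | no |
| Grip | yes | yes | no |
| Biodex torque | yes | no (three) | no |
| 6-minute walk | yes | no (single walk) | yes |

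**3. The plan's own figure.** With a difference of 8, an SD of 9, two-sided 5% and 80% power, the t-test calculation (d = 8/9 = 0.889) gives 20.87 per arm, so 21 per arm and 42 in total. The stated sample size reproduces, and this point does not affect it. The 21 per arm is used in step 5.

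**4. What extra attempts could do (illustration).** Assume independent, normally distributed attempts with the best one kept. The expected best of k attempts, in within-session SDs, is E(k) = ∫ x·k·φ(x)·Φ(x)^(k−1) dx:
- E(3) = 0.846, E(4) = 1.029, E(5) = 1.163.
- One extra attempt: 1.029 − 0.846 = 0.183 SD. Two extra: 1.163 − 0.846 = 0.317 SD.
- The documents give no within-session CV. At an assumed 5%, two extra attempts give 0.317 × 5% = 1.6%. At an assumed 10%, they give 3.2%.

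**5. Effect on the false-positive rate (illustration).** Let b be the between-arm bias in SDs of the change. The noncentrality is b·√(21/2), with 40 df and a two-sided 5% test.
- b = 0.1, 0.2 and 0.3 give false-positive rates of 6.2%, 9.7% and 15.8%.

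Steps 4 and 5 use different scales: b = 0.317 × (within-session SD ÷ SD of change). The documents do not give this ratio. If it is assumed to be 1/3, 2/3 or 1, b is about 0.11, 0.21 or 0.32. The false-positive rate is then roughly 6%, 10% or 16%, for two extra attempts per patient in one arm and none in the other.

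**6. The contradiction.** Read literally, the sentence on the highest of three trials keeps any fourth or later FVC, MIP or MEP attempt out of the analysis. The bias in step 4 is then zero for those measures. Read with the sentence that allows further attempts, later values count. The text does not settle which reading applies. The grip section has no three-trial sentence and simply records the maximum.

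**The case against.** **The status is disclosed.** The blinding section itself calls the physiotherapist non-blinded, and claims blinded assessment only for clinical and psychological evaluations. A reader might infer that the single-blind label conceals something; the text does not support that. What stands is that the label carries no exception and the results need one.

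**Not every test is exposed in the same way.** A reader might infer that the tester controls attempts and prompts throughout. Biodex contractions are fixed at three and the walk test is standardised. The fitness aim is also served by accelerometer data, which no assessor prompts. This objection is correct and narrows the point to the cells in the table.

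**The repeat rules are plateau rules and nominally the same in both arms.** Further attempts require continued improvement and, for the respiratory tests, no sign of fatigue. FVC also follows cited guidelines. This limits the discretion but does not remove it, because the tester judges whether the patient is still improving or tiring. It also means that step 4 does not model the protocol's rule: under a plateau rule, extra attempts occur only while values rise.

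**The primary outcome.** A reader might infer that the interview breaks the blinding of the MGQOL-15-F. The form is self-completed by patients who know their arm, so the psychologist's knowledge cannot change the score. The interview is about the impact of the disease and is held in both arms at all four visits. Visit order may also be left to the full protocol. Only a modest priming risk remains, plus some risk of disclosure for the interviewer-rated MINI and the interview.

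**Conclusion.** The point holds within limits. On the text shown, the M6 and M9 values of FVC, MIP, MEP, torque, grip and walk distance are taken by a tester who knows the arm, while M3 is blind. The exposure is greatest for FVC, MIP, MEP and grip through the number of attempts, and for the respiratory, Biodex and grip tests through encouragement. The contradiction in the pulmonary section stands whatever view is taken of blinding.

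The figure of 1.6% to 3.2% is not an estimate of the bias in this trial. It rests on assumed CVs, independent attempts and extra attempts in one arm only. For FVC, MIP and MEP it also requires that later attempts enter the analysis. A bias in favour of exercise is plausible, given the trial's hypothesis of benefit, but nothing in the document shows it.

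Severity is minor to moderate: mainly secondary outcomes are affected, and the repair is cheap.

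**What to change.** 1. Reconcile the two sentences in *Pulmonary function and respiratory strength*, and apply one attempt rule to both arms and all visits. For example, analyse the best of the first three attempts at M3, M6 and M9 for FVC, MIP, MEP and grip. M3 must be included, or the change score would mix two rules. Standardise encouragement for the respiratory, Biodex and grip tests, as is already done for the walk test.
2. At each visit, have the MGQOL-15-F and the other self-report forms completed and handed in before the semi-structured interview. This limits priming; it does not make a self-report by unblinded patients blind.
3. Report physiotherapist-measured outcomes as not assessor-blinded at M6 and M9.

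**Cost.** Wording in the assessment manual, visit order and one reporting sentence; no extra staff. A later, higher attempt would not be used. *Trial status* reports 32 patients already included. For them the first-three rule can be applied only if attempts were recorded one by one, which the article does not say. Where they were not, this should be reported. These steps reduce the scope for bias but leave the tester unblinded. A separate blinded evaluator at M6 and M9 would remove that, at the cost of staff.
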